### Data management and monitoring

2.10

All investigators will receive training in standardized operating procedures before the study starts. Data will be collected by community doctors using pilot-tested case report forms. Each patient's informed consent form and case report forms will be bound into 1 volume for management. The distribution of the moxa rolls and moxibustion boxes will also be strictly recorded. The software used to manage the electronic database will be Microsoft Access version 2016 (Microsoft Corporation, US), and the data will be doubly input and cross-checked by 2 independent investigators. All data in the database will be anonymized. When performing data analysis, the grouping will be concealed from the analysts.

An independent data monitoring committee will be established to monitor the quality of the data collection (eg, whether there are any incorrectly reported or missing data) and to ensure that any amendments or incomplete data are addressed in a timely manner. The committee will also have the right to plan an interim analysis (eg, when all patients have completed 6 months of follow-up) and to decide whether to discontinue the study based on the efficacy and safety results of the interim analysis.

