### Sample size calculation

2.11

We used the expected reduction in SBP as a reference and a sample size formula for continuous outcomes in nonrandomized controlled studies to estimate the minimum required sample size. Based on the results of our pilot observations and experts’ advice, we expect to measure a 5 mm Hg change in SBP with a standard deviation of 20 mm Hg. Setting the probabilities of type I error and type I error of 0.05 and 0.20, respectively, and considering a 20% attrition rate, the minimum sample size is calculated to be 140 per group. As we have sufficient funding, we increase the expected sample size to 300 cases per group to allow adjustment for more confounders.

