### Statistical analysis plan

2.12

The analyses of the primary outcomes will be performed in the intention-to-treat population where either patients in the control group who performed heat-sensitive moxibustion or patients in the heat-sensitive moxibustion group who stopped moxibustion during follow-up will still be kept in their original group. Meanwhile, we will also perform sensitivity analyses using the perprotocol population to test the robustness of the main analysis. All analyses of the secondary outcomes will be performed in the per-protocol population. We will decide whether to impute missing data and which method should be used to impute missing data based on the actual distribution of the missing data.

For categorical or ordinal variables, we will calculate frequencies and percentages as the descriptive statistics and compare the between-group differences using the chi-square test or the linear-by-linear association test. We will present the means with standard deviations/errors and medians with interquartile ranges for continuous variables with normal and skewed distributions, respectively; the independent *t* test or the Mann-Whitney *U* test will be used to compare 2 groups. The effects of heat-sensitive moxibustion on the outcomes will be inferred using analysis of covariance or a logistic regression model adjusted for age, course of hypertension, baseline SBP, comorbidities, education level, smoking status, drinking status, and types of antihypertensive drugs recoded as dummies. The effects will be measured as the mean difference or odds ratio with a 95% confidence interval, and *P*-values will also be calculated. In addition, we will test 2 subgroup hypotheses:

(1)the dose of moxibustion: ≥3 sessions/wk vs <3 sessions/wk;(2)whether the heat-sensitive sensation appears: yes vs no.

The significance level indicating a difference between groups and subgroups will be α = 0.05. We will use R version 4.0.2 (The R Foundation for Statistical Computing, Austria) to run all statistical analyses.

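### Section 2.10 leaves an efficacy interim and stopping to the committee's discretion beside an unadjusted 0.05; if 0.05 were also used to stop for benefit, the nominal type I error would be about 7% to 9.5%

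*Protocol article*

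**What the plan says.** Section 2.10 (Data management and monitoring) sets up an independent data monitoring committee, mainly to oversee data quality. It then adds a power: "The committee will also have the right to plan an interim analysis (eg, when all patients have completed 6 months of follow-up"). The same sentence lets the committee "decide whether to discontinue the study based on the efficacy and safety results of the interim analysis". The look is therefore optional, its timing is open, and efficacy is named as a ground for ending the study.

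Section 2.12 (Statistical analysis plan) gives one level for all comparisons: "The significance level indicating a difference between groups and subgroups will be α = 0.05". Section 2.11 (Sample size calculation) also uses 0.05 and makes no allowance for an interim look.

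Three other places bear on the point:
- Section 2.5 plans one year of self-administered moxibustion.
- Section 2.8 schedules blood pressure and the other outcome measurements at months 6 and 12.
- The Discussion names feasibility as a long-term intervention as an important purpose and one-year compliance as a main uncertainty.

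**The concern.** A look at efficacy that can end the study gives a second chance to declare a difference. Whether that raises the false-positive rate depends on the threshold used at the look. The article leaves the existence, timing and efficacy basis of the look to a decision made while data accrue, and the only level it states anywhere is an unadjusted 0.05. A study stopped on an early high would also tend to overstate the effect.

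The second issue is what an efficacy stop would gain. At the example time point every patient has been enrolled for at least six months, so no recruitment is saved. What is lost is follow-up towards month 12, which the one-year intervention and the long-term feasibility aim depend on. Patients also choose their own group, after lectures on anticipated efficacy (section 2.4). An early difference is therefore weak ground for stopping, and no patient is being randomised away from the treatment.

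**Working it through.** **Inputs from the article**
- Level: 0.05 (sections 2.11 and 2.12). Sidedness is not stated. I take it as two-sided because section 2.12 reports effects with a 95% confidence interval. The critical value is 1.96.
- Outcome times: months 6 and 12 (section 2.8). I take month 12, the end of follow-up, as the final analysis.
- Interim time: month 6, the article's own example.

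**Assumptions, not in the article**
- The look takes place, and 0.05 is used at it.
- The month-6 and month-12 test statistics have correlation ρ under the null. It is varied from 0.3 to 0.9.

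**Starting point.** With no efficacy look, the error for one outcome is the stated 5%. The article gives no overall error for a design with an interim, so there is no such figure to reproduce. The sample size figures do not enter this calculation.

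**Two looks at 0.05, one outcome**

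Overall error = 1 − P(|Z6| < 1.96 and |Z12| < 1.96), with (Z6, Z12) bivariate normal with correlation ρ.

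At ρ = 0 this can be done by hand: 1 − 0.95 × 0.95 = 0.0975. For other values, by numerical integration:

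| ρ | Overall two-sided error |
|---|---|
| 0.3 | 9.5% |
| 0.5 | 9.1% |
| 0.6 | 8.75% |
| 0.7 | 8.35% |
| 0.8 | 7.8% |
| 0.9 | 7.0% |

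These figures count a difference in either direction at either look. In the direction of benefit alone, the nominal 2.5% becomes 1 − P(Z6 < 1.96 and Z12 < 1.96). That is 4.8% at ρ = 0.3 and 3.5% at ρ = 0.9, so the proportional rise is the same (about 1.9 and 1.4 times).

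**Strict interim threshold (two-sided p < 0.001), final test left at 0.05**

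At ρ = 0: 1 − 0.999 × 0.95 = 0.051. By integration it is 5.1% at ρ = 0.3 and 0.5, and 5.0% from ρ = 0.6 upwards. The overall error is therefore 5.0% to 5.1% whatever the correlation.

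**Equal thresholds, for comparison.** To hold 5% with the same level at both looks, that level would have to be about 0.027 at ρ = 0.5 and 0.030 at ρ = 0.75. It depends on a correlation that is not known in advance, which the strict threshold avoids.

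**Follow-up at the example time point.** If the look falls when the last patient reaches month 6, that patient has six months still to run. Earlier enrollees have less, and some may already have finished. The length of recruitment is not stated, so the amount of 12-month data lost cannot be calculated.

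**The case against.** A reader might infer that the trial's type I error simply is 8% or 9%. The article does not support that. The committee has a right to plan a look, not a duty; month 6 is only an example; no interim threshold is stated; and the 0.05 in section 2.12 is not tied to the interim. With no look, or with a strict threshold, the error stays near 5%. The figure holds only under the stated conditions.

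The clause also does not say that the study would stop for proven benefit. Discontinuing on efficacy and safety results equally covers lack of effect or harm, and neither raises the false-positive rate for benefit. This objection stands, and the figure is confined to a stop for benefit.

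A boundary may sit in a committee charter or full analysis plan that is not shown. This stands too, so the absence of a boundary is not the complaint. What remains is what the article itself lays down: whether and when to look for efficacy, and whether to stop on it, are left to discretion during the trial beside a single unadjusted level. A boundary written elsewhere would not make that sentence in 2.10 a prespecified plan.

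A reader might also infer that an efficacy stop would remove months 7 to 12 altogether and leave the one-year question unanswerable. That goes too far, because early enrollees may already be at month 12.

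Finally, the design is nonrandomised and the Discussion names this as its main limitation. A nominal error rate is then not the largest threat to validity. This is fair, and it is why the point is rated as a modest one.

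**Conclusion.** The point holds in conditional form. If an efficacy look were used to stop for benefit at 0.05 and the final test were also at 0.05, the nominal two-sided type I error for systolic pressure alone would be about 7% to 9.5%. This rests on an assumed month-6/month-12 correlation of 0.9 to 0.3 and two-sided testing. It excludes confounding and the other primary outcomes (diastolic pressure and drug dose), which are a separate source of multiplicity.

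Independently of any threshold, stopping when all patients have reached month 6 would save no recruitment. It would leave outcome, compliance and safety data at 12 months incomplete for those not yet there. The risk is real, but it arises only if the committee uses its discretion in this way. Label: cheap improvement.

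**What to change.** Amend the sentence in section 2.10 to say that any interim analysis is for safety and data quality only, with no stopping for benefit.

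If an efficacy stop is to be kept, prespecify one look, at month 6, on systolic blood pressure, with a two-sided p < 0.001 threshold (Haybittle-Peto), and leave the final test at 0.05. The overall error is then about 5.0% to 5.1% for any correlation. Under this option 12-month data could still be cut short, but only after a very strong early result.

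The cost is one sentence in 2.10 and a matching line in the committee charter. No change to sample size or visits is needed, and safety monitoring is unaffected. The downside is that early stopping for benefit is given up or becomes very unlikely.

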### Sample size calculation

2.11

We used the expected reduction in SBP as a reference and a sample size formula for continuous outcomes in nonrandomized controlled studies to estimate the minimum required sample size. Based on the results of our pilot observations and experts’ advice, we expect to measure a 5 mm Hg change in SBP with a standard deviation of 20 mm Hg. Setting the probabilities of type I error and type I error of 0.05 and 0.20, respectively, and considering a 20% attrition rate, the minimum sample size is calculated to be 140 per group. As we have sufficient funding, we increase the expected sample size to 300 cases per group to allow adjustment for more confounders.

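### The stated minimum of 140 per group does not follow from the inputs printed beside it; a two-group comparison needs about 315 enrolled per group, so the planned 300 is roughly the requirement and not a twofold surplus

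*Protocol article*

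**What the plan says.** Section 2.11 (Sample size calculation) says that the size was found with "a sample size formula for continuous outcomes in nonrandomized controlled studies", which it does not name. The inputs follow: "we expect to measure a 5 mm Hg change in SBP with a standard deviation of 20 mm Hg", then "Setting the probabilities of type I error and type I error of 0.05 and 0.20, respectively", and "considering a 20% attrition rate". The result is that "the minimum sample size is calculated to be 140 per group". The next sentence cites sufficient funding and says "we increase the expected sample size to 300 cases per group to allow adjustment for more confounders".

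Section 2.12 (Statistical analysis plan) compares two groups and measures continuous effects as a mean difference from analysis of covariance, adjusted for baseline SBP and other covariates. On the test level it says "The significance level indicating a difference between groups and subgroups will be α = 0.05". Neither section says whether the test is one-sided or two-sided. Section 2.11 does not say whether the 5 mm Hg is a between-group difference or a within-group change, and gives no covariate correlation or R-squared.

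**The concern.** Apart from sidedness, every quantity needed to check the minimum is printed beside it, and the result is less than half of what those quantities imply for the between-group comparison that section 2.12 plans. This is not a detail left to a fuller document: the article states both the inputs and an answer that disagrees with them.

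Two statements rest on the figure. One is that 140 per group is adequate at the stated error rates. The other is that 300 per group is more than twice what is needed (300/140 = 2.1), with the excess available for confounder adjustment. That second statement matters in a study where patients choose their own group, because adjustment is the main defence against bias. A reader should be able to see how much precision is really available for it.

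**Working it through.** **Inputs** (section 2.11 unless noted)
- Difference d = 5 mm Hg, read as between-group because section 2.12 estimates a between-group mean difference.
- SD s = 20 mm Hg.
- Type I error 0.05. The 0.20, also labelled type I, is read as type II error, so power is 80%.
- Attrition 20%, so enrolled = evaluable/0.8.
- Assumptions: equal groups, since one figure is given per group; two-sided test, with one-sided also tried.

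**Attempt to reproduce 140**

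Two groups: n = 2(z_α + z_β)² s²/d², with s²/d² = 400/25 = 16.
- Two-sided: 2 × (1.960 + 0.842)² × 16 = 251.2, so 252 evaluable; 252/0.8 = 315 enrolled. Inflating the unrounded 251.2 gives 314. Multiplying by 1.2 instead of dividing by 0.8 gives 302.4, so 303.
- One-sided: 2 × (1.645 + 0.842)² × 16 = 197.8, so 198 evaluable; 198/0.8 = 247.5, so 248 enrolled (238 with the 1.2 multiplier).

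One sample or paired, in case the 5 mm Hg is a within-group change: n = (z_α + z_β)² s²/d².
- Two-sided: 125.6, so 126 evaluable; 126/0.8 = 157.5, so 158 enrolled (152 with the multiplier).
- One-sided: 98.9, so 99 evaluable; 99/0.8 = 123.75, so 124 enrolled (119 with the multiplier).

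None of these gives 140.

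**What 140 and 300 deliver**

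Two-sided power ≈ Φ(d/(s√(2/n)) − 1.960). Detectable difference at 80% power = 2.802 × s√(2/n).

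| Enrolled per group | Evaluable per group | Power | Detectable difference |
|---|---|---|---|
| 140 | 140 × 0.8 = 112 | Φ(1.871 − 1.960) = 46% | 7.5 mm Hg |
| 140, no attrition | 140 | Φ(2.092 − 1.960) = 55% | 6.7 mm Hg |
| 300 | 300 × 0.8 = 240 | Φ(2.739 − 1.960) = 78% | 5.1 mm Hg |

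The noncentral t gives 46.1%, 55.0% and 78.0%. A one-sided test with 112 evaluable gives Φ(1.871 − 1.645) = 59%.

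**What would make 112 evaluable sufficient**

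One of the following would be needed: an SD of about 13.4 mm Hg, a difference of about 7.5 mm Hg, or covariates explaining 1 − 112/251.2 = 55% of the variance. Section 2.11 states none of them.

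**What would bring 300 enrolled to 80% power**

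Covariates would have to explain about 1 − 240/251.2 = 4.5% of the variance, net of any variance inflation caused by correlation between group and covariates.

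**The case against.** The strongest reply is that nobody plans a trial of 140 per group. The planned size is 300, which has about 78% power against a target of 80%, and by the cruder multiplication convention 300 is within a few patients of the requirement (303). The planned estimate is also adjusted for baseline SBP, and an R-squared of about 4.5% would close the gap. All of this stands, and it limits the practical effect. It does not rescue the 140, and it does not make 300 a twofold surplus. Nor can planned adjustment explain the 140, because section 2.11 offers adjustment as the reason for going beyond that figure.

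Three stronger readings are tempting, and the article does not support them.

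- *The authors used a single-group formula with the wrong attrition rate.* A reader might infer this because 125.6/0.9 = 139.5. It requires 10% loss, which contradicts the stated 20%. The 125.6 is also just half of 251.2, so other slips give the same number. A one-sample, one-sided calculation at 90% power without attrition comes close as well (137), and it too contradicts the stated inputs. With the formula unnamed, the origin is unknown.
- *The trial will have less than an even chance of detecting its target.* The 46% applies only if enrolment ended at 140 per group. Section 2.11 plans 300, and the interim provision in section 2.10 concerns efficacy and safety results, not stopping at the minimum.
- *Nothing is spare at 300.* That ignores the planned covariance adjustment. As an assumed example, R-squared of 10% at 240 evaluable gives Φ(2.739/√0.9 − 1.960) = 82%. Correlation between group and confounders works the other way: an assumed variance inflation of 1.2 with no gain in R-squared gives Φ(2.739/√1.2 − 1.960) = 71%. The article gives neither quantity, so the net room for adjustment is unknown.

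**Conclusion.** Wrong as written. The minimum of 140 per group is less than half of the roughly 315 that its own inputs require for a two-sided two-group comparison, and no one-sided or single-sample variant with the stated attrition reproduces it.

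The planned 300 per group is about the unadjusted requirement: roughly 2 power points below target, with a detectable difference about 0.1 mm Hg above the 5 mm Hg aimed at. The error therefore lies in the justification much more than in the operating design.

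The conclusion assumes equal groups, a between-group difference of 5 mm Hg, 0.20 as the type II error, and no recovery of information from the 20% lost. Sidedness does not alter it. If the 140 rests on inputs that the article does not print, those inputs need to be stated.

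**What to change.** In section 2.11:

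- Withdraw 140 as the minimum.
- State that the 5 mm Hg is a between-group difference and that the test is two-sided (if so intended), with an unadjusted requirement of about 252 evaluable, or 315 enrolled, per group.
- Justify the planned 300 explicitly. Otherwise the text would show a planned size below its own minimum. Either report what 300 delivers (240 evaluable, about 78% unadjusted power, about 5.1 mm Hg detectable at 80% power), or state the covariate R-squared, net of variance inflation from group-confounder correlation, under which 300 reaches 80%.
- Reword the sentence that presents the step from 140 to 300 as room for more confounders.
- Correct the second type I error to type II.

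The cost is a rewording of one section. No extra patients are needed and the analysis does not change. The stated power becomes slightly less favourable.

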### Statistical analysis plan

2.12

The analyses of the primary outcomes will be performed in the intention-to-treat population where either patients in the control group who performed heat-sensitive moxibustion or patients in the heat-sensitive moxibustion group who stopped moxibustion during follow-up will still be kept in their original group. Meanwhile, we will also perform sensitivity analyses using the perprotocol population to test the robustness of the main analysis. All analyses of the secondary outcomes will be performed in the per-protocol population. We will decide whether to impute missing data and which method should be used to impute missing data based on the actual distribution of the missing data.

For categorical or ordinal variables, we will calculate frequencies and percentages as the descriptive statistics and compare the between-group differences using the chi-square test or the linear-by-linear association test. We will present the means with standard deviations/errors and medians with interquartile ranges for continuous variables with normal and skewed distributions, respectively; the independent *t* test or the Mann-Whitney *U* test will be used to compare 2 groups. The effects of heat-sensitive moxibustion on the outcomes will be inferred using analysis of covariance or a logistic regression model adjusted for age, course of hypertension, baseline SBP, comorbidities, education level, smoking status, drinking status, and types of antihypertensive drugs recoded as dummies. The effects will be measured as the mean difference or odds ratio with a 95% confidence interval, and *P*-values will also be calculated. In addition, we will test 2 subgroup hypotheses:

(1)the dose of moxibustion: ≥3 sessions/wk vs <3 sessions/wk;(2)whether the heat-sensitive sensation appears: yes vs no.

The significance level indicating a difference between groups and subgroups will be α = 0.05. We will use R version 4.0.2 (The R Foundation for Statistical Computing, Austria) to run all statistical analyses.

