Heat-sensitive moxibustion, an innovative acupoint stimulation therapy, has been developed based on traditional moxibustion in recent decades.^[12]^ The major innovation in heat-sensitive moxibustion therapy is the discovery of heat-sensitive acupoints.^[13]^ Researchers find that when persons suffer from diseases, heat-sensitive points appear on their body, and these points may differ from the classic acupoints in terms of location. When moxibustion is applied to heat-sensitive acupoints, patients experience unusual feelings (referred to as “heat-sensitive sensations”), including penetrating heat, expanding heat, heat transfer, distant heat, deep heat, and other feelings unrelated to heat (such as soreness, bloating, and numbness).^[12]^ It has been proven that heat-sensitive moxibustion is more efficacious than traditional moxibustion for multiple diseases, such as lumbar disc herniation and bronchial asthma.^[14,15]^

In principle, heat-sensitive moxibustion should be effective for hypertension. However, there is no high-quality evidence regarding the effects of heat-sensitive moxibustion on hypertension to date, and all current evidence regarding other acupoint stimulation therapies, including traditional moxibustion for hypertension, was generated in a hospital setting. For a chronic disease such as hypertension, compliance with treatment will be poor if patients are required to go to the hospital regularly to receive acupoint stimulation therapy. In contrast, patients can administer moxibustion treatment to themselves or with the help of their family at home after receiving brief training. Therefore, we assume that heat-sensitive moxibustion may be a feasible approach to the management of hypertension in a community setting. To verify this hypothesis, we will conduct a nonrandomized controlled study in multiple communities to evaluate the pragmatic effectiveness and safety of heat-sensitive moxibustion self-administration in patients with primary hypertension.

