#### Secondary outcomes

2.6.2

(1)Quality of life will be assessed by a validated patient-reported outcome scale,^[18]^ which includes 27 items and assesses the impacts of hypertension on the 3 dimensions of quality of life, namely, the physical dimension (18 items), psychological dimension (4 items), and family-social dimension (5 items). Each item is divided into 5 categories, with each category receiving 0 to 4 points in sequence. A higher score indicates a worse quality of life. The total score equals the sum of the score of each item, ranging from 0 to 108 points. The detailed content of the scale is provided in the Supplemental Content (http://links.lww.com/MD/E870). We will also analyze the scores of individual dimensions separately.(2)Indicators related to diabetes mellitus, including changes in fasting blood glucose (mg/dl) and hemoglobin A1c (%), will be assessed.(3)Indicators related to dyslipidemia, including changes in total cholesterol (mg/dl), triglycerides (mg/dl), low-density lipoprotein cholesterol (mg/dl), and high-density lipoprotein cholesterol (mg/dl) levels, will be assessed.(4)Indicators related to hypertensive renal disease, including urinary albumin (g/l) and serum creatinine (μmol/l) levels, will be assessed.(5)Patient compliance will be determined. Patient compliance will be deemed poor if a patient administers heat-sensitive moxibustion fewer than 8 times per month. The proportion of patients with poor compliance will be assessed.

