In 2017, the government of Xiashan District in Weifang city in Shandong Province tried for the first time to popularize heat-sensitive moxibustion as a daily health care method for all residents of the town. The measures taken to popularize the knowledge of heat-sensitive moxibustion included building a community center dedicated to providing free sessions of heat-sensitive moxibustion, organizing expert lectures, training patients on-site, and providing free moxibustion materials. After 2 years of efforts, the popularization work achieved satisfactory results – heat-sensitive moxibustion was practiced by 67% of the total population of 62,000 people. In addition, the per capita medical expenditure decreased by 49.8% and the number of annual outpatient consultations decreased by more than 16.7% compared with the values 2 years before.^[21]^ Unfortunately, no rigorous evidence was obtained regarding the effects of heat-sensitive moxibustion on hypertension with the exception of scattered case reports published during the popularization campaign. Learning from the successful experience in Shandong Province, the government of Jiangxi Province started to promote a public health project called “Everyone Uses Heat-sensitive Moxibustion, Everyone Enjoys Health” in several cities in 2019. Currently, the project is progressing smoothly. It could provide a favorable climate for the recruitment of participants and the successful completion of this study.

This study has potential limitations. The reduction of internal validity caused by the nonrandomized design is the main limitation. Although we have expanded the expected sample size as much as possible and will adjust for multiple confounders in the statistical analysis, the bias caused by unknown confounders cannot be completely avoided. However, the extrapolation of the results of this study, as a major advantage of a pragmatic study, will be enhanced. Another limitation is that it may be difficult for patients to remain compliant with the heat-sensitive moxibustion protocol for 1 year, and poor compliance will introduce bias. However, an important purpose of this study is to evaluate the feasibility of heat-sensitive moxibustion self-administration as a long-term intervention in patients in the community with hypertension. If compliance is poor, it will show that this is not a feasible strategy.

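### Analysing the poor-compliance proportion only in the per-protocol population understates it, and the other secondary outcomes lose their as-assigned comparison

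*Protocol article*

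**What the plan says.** Section 2.12 treats the two classes of outcome differently. The primary outcomes are analysed by intention-to-treat, where "patients in the heat-sensitive moxibustion group who stopped moxibustion during follow-up will still be kept in their original group", and controls who took up moxibustion likewise stay in the control group. Per-protocol has a supporting role there: "we will also perform sensitivity analyses using the perprotocol population to test the robustness of the main analysis". For the secondary outcomes the rule is "All analyses of the secondary outcomes will be performed in the per-protocol population". It has no exception and no intention-to-treat companion analysis.

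Section 2.6.2 lists compliance as secondary outcome (5): "Patient compliance will be deemed poor if a patient administers heat-sensitive moxibustion fewer than 8 times per month", and "The proportion of patients with poor compliance will be assessed".

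The Discussion says that "an important purpose of this study is to evaluate the feasibility of heat-sensitive moxibustion self-administration as a long-term intervention", and gives the inference to be drawn: "If compliance is poor, it will show that this is not a feasible strategy". The Introduction states the overall aim, which is to "evaluate the pragmatic effectiveness and safety of heat-sensitive moxibustion self-administration in patients with primary hypertension".

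The article does not define the per-protocol population. Section 2.5 lets patients change how much moxibustion they do, provided they report it truthfully.

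**The concern.** A compliance proportion is informative only if its denominator includes the people who did not comply. Section 2.12 computes it in a population selected, at least in part, on having complied. The resulting feasibility estimate is biased in the favourable direction, although the Discussion says feasibility is to be judged on it.

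The other secondary outcomes have a related problem. Groups are formed by patient preference (section 2.4), so the comparison already carries self-selection. Restricting it to patients who kept to their regimen adds a second selection made after baseline. The exclusion criteria also differ between arms: in the moxibustion group a patient leaves the set by stopping, in the control group by taking moxibustion up. The baseline covariates listed in section 2.12 cannot be relied on to remove that difference.

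**Working it through.** The article gives no figure for the poor-compliance share or for per-protocol exclusions, so there is nothing to reproduce. The check is first a reading of the text and then an illustration.

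**Does the per-protocol set drop patients whom outcome (5) must count?**

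1. The intention-to-treat set in section 2.12 is characterised by keeping two kinds of patient: moxibustion patients who stopped and controls who used moxibustion.
2. The per-protocol set is offered as the contrast, so it drops them by implication.
3. A patient who has stopped does 0 sessions in each full month that follows. Since 0 is below 8, that patient meets the section 2.6.2 definition of poor compliance.
4. Some poor compliers are therefore removed before their proportion is calculated.

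**By how much does this lower the proportion?**

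Inputs:
- N = 300 moxibustion patients (section 2.11).
- p = true share with poor compliance (assumption; not in the article).
- f = fraction of poor compliers excluded from the per-protocol set (assumption; not in the article).
- No good compliers are excluded (simplifying assumption).

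Reported share = (Np − Npf) / (N − Npf) = p(1 − f) / (1 − pf).

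For p = 30% there are 300 × 0.30 = 90 poor compliers:
- f = 0.5: 45 removed, 45 / 255 = 17.6%.
- f = 0.75: 67.5 removed, 22.5 / 232.5 = 9.7%.
- f = 1: 90 removed, 0 / 210 = 0%.

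Over a range of assumed true shares:

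| True share p | f = 0.5 | f = 0.75 | f = 1 |
|---|---|---|---|
| 10% | 5.3% | 2.7% | 0% |
| 30% | 17.6% | 9.7% | 0% |
| 50% | 33.3% | 20.0% | 0% |

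**Direction.** The reported share is below p whenever p(1 − f) < p(1 − pf). For p above 0 this means f > pf, which holds for every f above 0 and p below 1. If some good compliers are also excluded, the share is still too low as long as poor compliers are excluded at the higher rate.

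**With the whole moxibustion group as denominator**, f = 0 and the formula returns p.

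**The case against.** The strongest reply is that the per-protocol set is undefined and that a condensed article may leave its definition to a fuller document. Nothing ties the set to the 8-session threshold. Because section 2.5 allows patients to adjust their dose, someone doing one session a week may be acting within the protocol. That patient could stay in the per-protocol set and be counted as a poor complier. This stands, and it limits the claim. A reader might infer that the reported proportion is forced to about zero by construction. The article does not support that: it would require every poor complier to be excluded, which is only the f = 1 column.

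A reader might also infer that the exclusions fall almost entirely on the moxibustion arm. That is not supported either. Section 2.12 names control crossovers as deviators, section 2.5 bars controls from moxibustion and both groups from other acupoint therapies, and the Discussion describes a public campaign in the province that makes crossover plausible. The article shows that the exclusion criteria differ between arms, not how the numbers will split.

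Finally, both primary outcomes are analysed by intention-to-treat, so the main effectiveness conclusion is not undermined.

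The reply does not remove the conflict. Leaving the definition to another document does not change what section 2.12 implies about patients who stopped. If the authors mean to report compliance in everyone who entered the moxibustion group, the sentence needs an exception that it does not contain.

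**Conclusion.** The point holds in a limited form. As written, the plan excludes at least the patients who stopped moxibustion from the outcome that should count them, and so understates poor compliance. This conflicts with the feasibility purpose in the Discussion. The direction follows from the text, given the implied exclusion of stoppers. The size does not: the 17.6%, 9.7% and 0% for a true 30% rest on assumed values of p and f.

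For quality of life, glucose, lipids and renal markers, the fault is a population choice that gives up the as-assigned comparison, which the protocol keeps for its primary outcomes. It fits poorly with the pragmatic aim, but it concerns supportive results only. The compliance outcome is the more serious part, because a stated purpose of the study depends on it.

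**What to change.** Change section 2.12 as follows.

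- **Compliance.** Report the poor-compliance proportion with all patients who entered the moxibustion group as the denominator. Count patients who stopped as poor compliers from the month they stop. Withdrawal is allowed for any reason (section 2.9), so show withdrawals for reasons unrelated to moxibustion both ways, as poor compliers and as missing. How to count them is a choice, and the two results bound it.
- **Other secondary outcomes.** Analyse them by intention-to-treat, with per-protocol as the sensitivity analysis, as for the primary outcomes.
- **Per-protocol set.** Define it for both groups, and say how it relates to the 8-session threshold and to the dose adjustment allowed in section 2.5.

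Compliance is already assessed at the regular monthly visits (section 2.8), so no new data collection is needed. There are two costs. Secondary effects may look smaller. Patients who leave may also lack month 6 and 12 laboratory and quality-of-life values, so the missing-data decision that section 2.12 leaves open would have to cover these outcomes as well.
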